#### Postoperative follow-up schedule

Patients will be followed for 3-year after surgery. Follow-up will consist of a physical examination and blood tests, including carcinoembryonic antigen (CEA) levels every 6 months after surgery. Chest X-ray and abdomino-pelvic CT every 6 months after surgery, chest CT will be performed every 6–12 months, and colonoscopy performed at 6–12 months and 24–36 months after surgery (Table 1).

**Table 1 Tab1:** Follow-up schedule and study procedure for study cohort

Documentation	Restaging	LE vs. TME	Visit 1	Visit 2–6
Study procedures	Screening	Surgery	Checking complications	Routine checkup
Period after pre-CRT	4–8 weeks	4–8 weeks	8–16 weeks	Every 6 months after Op.
Getting permission	●			
Screening	●			
Assigning serial number	●			
Demographics	●			
Physical exam	●		●	●
Heart/ lung evaluation	●			
Chest CT	●			● (Selective)
APCT	●			●
MR, rectal cancer	●			● (Selective)
Endoscopy	●			● (Selective)
Laboratory test	●		●	●
Endorectal sonography	●			
Manometry/questionnaire	●			● (Selective)
Checking complications			●	●
Selection of surgery type		●		

*Pre-CRT* Preoperative chemoradiotherapy, *Op*., Operation, *LE* Local excision, *TME* Total mesorectal excision, *CT* Computed tomography, *APCT* Abdomino-pelvic CT, *MR* Magnetic resonance

#### Primary outcome

The primary endpoint of the current study is the rate of postoperative complications. Postoperative events occurring up to 30 days after surgery will be evaluated by the Clavien-Dindo Classification, any events grade 2 or higher will be considered postoperative complications.

#### Secondary study endpoints

1. Disease-free survival rate (%), overall survival rate (%) and recurrence rate (%) at 3 years.

2. Functional outcomes, including quality of life (EORTC-E030) and score of fecal incontinence (Wexner’s score) at 6, 12 and 24 months after surgery.

3. Rate of permanent stoma formation (%) at 3 years.

4. Accuracy of mrTRG (positive predictive value and negative predictive value).

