## Background

In the treatment of rectal cancer, total mesorectal excision (TME) improves oncologic outcomes and adding preoperative chemo-radiotherapy (pre-CRT) to TME has been shown to effectively improve local control [1–4]. For this reason, pre-CRT followed by TME is recommended for patients with locally advanced mid-to-low rectal cancer [5–9]. However, significant complications are associated with TME, including anastomotic leak, sexual and urinary dysfunction, and frequent stool passage, on top of the peri-operative morbidity associated with all major surgery [10–12]. In addition, abdominoperineal resection (APR) involves a permanent stoma and low anterior resection (LAR) often involves at least a temporary stoma [8, 12, 13]. The decision of a surgical strategy must take oncologic outcomes, postoperative complications, and quality of life into account.

For patients with favorable responses to pre-CRT, organ-preserving strategies such as local excision (LE) and watchful waiting are becoming more accepted [14–19]. There has been some debate regarding the oncologic safety of LE following pre-CRT in advanced mid-to-low rectal cancer [14–18]. LE following pre-CRT for advanced rectal cancer could be a particularly good option for patients showing a complete pathologic response and achieving tumor regression not only in the primary tumor but also in the mesorectal metastatic lymph nodes [20–24]. Although the tumor regression grade (TRG) obtained using high-resolution rectal magnetic resonance imaging (mrTRG), as proposed by the MERCURY study group, correlated with the pathologic TRG [20, 21, 23, 24], mrTRG did not reflect the pathologic T status. A recent study from our institution showed that a status of mrTRG1 predicted a pathologic complete remission (pCR) with 60.6% accuracy and the projected completion TME rate of mrTRG1 was 25.6%. This results suggests that LE, compared with watchful wait, is more likely to result in pCR [25].

There have been several reports on the feasibility of performing LE following pre-CRT, most of which are focused on either clinical T2–3 rectal cancer or on cases of pCR [26–28]. However, the oncologic safety of LE in patients with a pathologic early T status after pre-CRT has not been established [29]. Therefore, data on long term outcomes with respect to the pathologic status and the type of surgery in patients with locally advanced rectal cancer is needed.

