### Secondary outcomes measures

Secondary outcomes will be as follows:Oncologic outcomes: 3-year disease-free survival (% DFS), 3-year overall survival (% OS), and recurrence rate (%).Functional outcomes: quality of life, as measured using EORTC QLQ-C30 (version 3) and rectal function, as measured using manometry, low anterior resection syndrome (LARS) score, and the Wexner Fecal Incontinence Score.The rate of permanent stoma formation (%).Factors affecting complete remission and the accuracy of mrTRG.Oncologic outcome in patient subgroups.

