### Treatment strategies

#### Standard care of the control arm

TME is the standard treatment and is undertaken 6–8 weeks after the completion of pre-CRT. All operations were performed by experienced colorectal surgeons (> 100 rectal cancer cases per year). Temporary diverting ileostomy is occasionally performed in cases of a very low anastomotic level with considerable tension, air leak, or severe comorbidities. We do not perform lateral lymph node dissection routinely.

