In terms of postoperative complications, only one patient (2.1%) in our previous study developed a postoperative complication (perianal fistula) that required prolonged hospitalization [27]. In a recent prospective study of LE in patients with T2 rectal cancer, surgery-related adverse events above grade 3 occurred in 16 patients (21%) and grade 1 or 2 complications occurred in 50 patients (65%) [26]. Although complications of LE after pre-CRT are generally less severe than complications of TME, the rate of overall complications including dehiscence of the rectal suture line resulted from anal pain are higher than TME after pre-CRT [26]. Based on the assumption that the oncologic outcomes of LE and TME are similar for patients with a favorable response (mrTRG 1 or 2) after pre-CRT, further prospective studies on surgical outcomes in LE after pre-CRT are needed.

Pre-CRT followed by LE causes minimal loss of anorectal function and quality of life, similar to watchful waiting [26]. TME results in postoperative loss of anorectal, urinary and sexual function, and also carries the risk of permanent stoma formation [10]. In mid-to-low advanced rectal cancer, the use of pre-CRT has decreased the rate of permanent stoma formation; however, in our recent study, approximately 30% of patients receiving TME after pre-CRT did develop a permanent stoma [27]. A recent prospective study suggested that pre-CRT followed by LE might be an alternative to TME for patients with rectal cancer who have a favorable response to pre-CRT or who seek organ preservation because the Fecal Incontinence Severity Index (FISI) score and the Functional Assessment of Cancer Therapy-Colorectal (FACT-C) scores did not substantially decrease after surgery [26].

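### The Wexner, LARS and manometry comparisons have no interpretable value in patients with a stoma, so a test on available scores is not a randomised comparison and probably understates any LE benefit in bowel function.

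*Protocol article*

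**What the plan says.** The protocol article describes the functional endpoints in two places. Under Secondary outcomes measures, rectal function is "measured using manometry, low anterior resection syndrome (LARS) score, and the Wexner Fecal Incontinence Score". Under Secondary study endpoints, item 2 is "Functional outcomes, including quality of life (EORTC-E030) and score of fecal incontinence", the latter by the Wexner score, with assessments set at 6, 12 and 24 months. Item 3 of the same list is "Rate of permanent stoma formation (%) at 3 years". Neither place limits the bowel-function measures to patients with restored continuity or says how a patient with a stoma counts.

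Under Data analysis, continuous outcomes are compared by Student's t-test or the Mann-Whitney test, and secondary endpoints use the modified ITT set. Table 1 marks manometry and questionnaires as selective at the postoperative visits.

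On stomas after TME, the Background says that "abdominoperineal resection (APR) involves a permanent stoma and low anterior resection (LAR) often involves at least a temporary stoma". The section on the control arm says "Temporary diverting ileostomy is occasionally performed in cases of a very low anastomotic level". The Discussion reports that, in the institution's own recent study, "approximately 30% of patients receiving TME after pre-CRT did develop a permanent stoma".

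**The concern.** An incontinence score, a LARS score and anal manometry presuppose that stool passes through the anus. A patient with an end stoma, or with a diverting ileostomy still open at the visit, has no interpretable value. The named two-group tests can use only patients who have a value. In the TME arm that leaves out patients after APR and anyone still diverted. In the LE arm it leaves out few. Having a score is then partly a consequence of the allocated operation, and the groups being compared are no longer those formed by randomisation.

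Preserved anorectal function is one of the main arguments the Background and Discussion give for LE. A comparison limited to TME patients with continuity could report similar bowel function while a sizeable share of the TME arm has a stoma. The separate stoma endpoint does not repair this. It is counted at 3 years, while Wexner is assessed at 6, 12 and 24 months. It also does not cover temporary stomas open at those visits.

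**Working it through.** **Inputs from the protocol article.** Per arm: 67 (Sample size calculation; 140 enrolled, so 70 per arm before dropout). Permanent stoma after TME: about 30% (Discussion). This is a cited observed rate that cannot be recomputed from the text. Projected completion TME in mrTRG1: 25.6% (Background).

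**Assumptions.** A range of 20% to 40% around the 30%. An LE-arm stoma rate, which the article does not give.

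**1. TME patients without an interpretable score.**
- 0.30 × 67 = 20.1, leaving about 47 (0.30 × 70 = 21, leaving 49)
- 0.20 × 67 = 13.4 and 0.40 × 67 = 26.8, so 13 to 27

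The number at 6 months is higher if temporary ileostomies are still open. No rate or closure time is given.

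**2. Direction of the bias.** Assume for illustration a mean Wexner score of 8 in TME patients with continuity and 5 in LE, higher being worse. The available-score difference is 8 − 5 = 3. The full-arm TME mean is 0.7 × 8 + 0.3 × w, where w is the value given to a stoma.
- w = 20 (taken as worst): 5.6 + 6.0 − 5 = 6.6
- w = 8 (same as the others): 5.6 + 2.4 − 5 = 3.0
- w = 0 (counted as no leakage): 5.6 + 0 − 5 = 0.6

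So available scores understate the LE benefit if a stoma counts as a bad bowel outcome, and overstate it if a stoma counts as no leakage.

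A second view supposes that the stoma patients would otherwise have been the worst-functioning 30% on a normal scale. Dropping them improves the TME mean by φ(0.524)/0.70 = 0.348/0.70 = 0.50 SD. If stoma is unrelated to function, the shift is 0.

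**3. What a rank analysis with stoma as worst would show.** Let p and q be the stoma rates in the TME and LE arms, with equal function among patients with continuity. The available-score test then targets P(LE better) = 0.50. Over all patients, P = (1 − q)p + 0.5(1 − q)(1 − p) + 0.5qp = 0.5 + 0.5(p − q). The null standard error is √(135/(12 × 67 × 67)) = 0.050.
- p = 0.30, q = 0: P = 0.65, z = 3.0
- p = 0.30, q = 0.05: P = 0.625, z = 2.5
- p = 0.30, q = 0.256 × 0.30 = 0.077, if completion TME carries the same stoma rate: P = 0.61, z = 2.2

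Keeping q = 0.256 × p over the assumed range:
- p = 0.20: q = 0.051, P = 0.5 + 0.5 × 0.149 = 0.57, z = 1.5
- p = 0.40: q = 0.102, P = 0.5 + 0.5 × 0.298 = 0.65, z = 3.0

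These values re-express the assumed difference in stoma rates. They show how far the two analyses can part, and are not evidence about bowel function itself.

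**The case against.** The strongest reply is that the article is condensed. Nothing in it says that stoma patients will be dropped, and a scoring rule for a secondary questionnaire may well stand in the full protocol or analysis plan. That is fair, and the point should not be read as saying that the plan prescribes exclusion. What remains is that the article fixes measures that need an anal outlet, assessment times for Wexner, and a two-group test, while describing a control operation that often leaves a stoma. If stoma status is not recorded at each visit, no later analysis plan can fully recover it.

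Other parts of the reply also stand:
- A reader might infer that the whole functional comparison loses its stoma patients. It does not, because the EORTC quality-of-life questionnaire can be completed with a stoma. Nor is the stoma outcome lost to the trial, since item 3 counts permanent stomas.
- A reader might infer that the LE benefit is certainly understated. The documents do not establish that: the sign depends on how a stoma is valued. *Probably* rests on the Background and Discussion treating a stoma as a harm of TME.
- The 30% is not specific to mrTRG 1 or 2, and it is a permanent-stoma rate, not prevalence at a visit.
- LE-allocated patients are not free of stomas, because some will have completion TME.
- Ranking a stoma as worst is a value judgement. Reporting continuity-only scores beside the stoma rate is a legitimate analysis if it is labelled for what it is.

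**Conclusion.** The point holds in a limited form. For Wexner, LARS and manometry, a test on available scores compares LE with TME patients selected by an event after randomisation. At the article's 30%, about 20 of 67 TME patients would have no interpretable value (13 to 27 at 20% to 40%), against few in the LE arm: about 5 of 67 (0.077 × 67 = 5.2) under the completion-TME assumption. Such a test probably understates any LE benefit in bowel function. The size of the bias is not known. The mean shift runs from 0 to 0.5 SD under the normal-score model, and the sign reverses if a stoma is scored as no leakage.

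The conclusion rests on the institution's rate applying at least roughly to this population, and on stomas being clearly less frequent in the LE arm. The quality-of-life comparison, the primary endpoint and the sample size are not touched.

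**What to change.** - **Data.** Record stoma status (none, temporary, permanent) at 6, 12 and 24 months.
- **Analysis.** In Secondary study endpoints and Data analysis, add for Wexner and LARS a Mann-Whitney rank comparison at each time point, by allocated arm, over all randomised patients alive, with a stoma at that visit ranked worst. The test is already named in the plan.
- **Presentation.** Show it beside the comparison among patients with continuity. Label the latter, and the manometry comparison, as conditional on a post-randomisation outcome, and read them together with the stoma rate.
- **Allocation.** For this analysis, keep LE-allocated patients who have or decline completion TME in their allocated arm. The section on the experimental arm evaluates the former with the TME group and excludes the latter from the study, so the two texts must be reconciled.

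The cost is one field per visit and a few sentences of analysis text. The downside is that a rank result is less directly read in score points and treats a stoma as the worst bowel outcome by convention. For that reason neither analysis should be reported alone.

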### Study population

Patients who were diagnosed with pathologically confirmed rectal adenocarcinoma < 8 cm from the anal verge with clinically T3 or N+ before pre-CRT and an mrTRG grade 1 or 2 based on post-CRT images will be eligible for the study when they meet the following inclusion criteria:Male and female patients between the age of 20 and 80;Good performance status (ECOG performance status < 2);Capable of providing informed consent.

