#### Preoperative restaging

For assessing the pre-CRT response, digital rectal examination, sigmoidoscopy, abdomino-pelvic computed tomography (CT), chest CT, trans-rectal ultrasonography and MRI were performed within 2 weeks before surgery. Two board-certified abdominal radiologists independently assessed the response to CRT on post-CRT MRI using mrTRG (1–5) according to published definitions: 1, complete radiologic response; 2, dense fibrosis with no obvious residual tumor; 3, > 50% fibrosis or mucin with visible residual tumor; 4, small areas of fibrosis or mucin but mostly tumor, or tumor growth; 5, same appearance as baseline. The enrollment of a study cohort requires a multidisciplinary team including a colorectal surgeon, medical oncologist, radiation oncologist, and radiologist.

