#### Randomization and data management

After checking the response of pre-CRT, the participants with mrTRG 1 or 2 tumor will be assigned using random-number table with sealed envelopes by an external research worker who control the data. According to mrTRG 1 or 2, the allocation sequence will be stratified. The external research worker will collect the data and a statistician who provided the sample size calculation and data analysis plan will be analyze the data. The data entry, coding, security and storage with backup will be processed by the external research worker and simultaneously the statistician will check the accuracy and the value of the data. After finishing the collection of data, the external research worker, the statistician will access the dataset and investigators will access after analyses of the dataset.

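### Because only mrTRG 1 and 2 are enrolled, the NPV in secondary endpoint 4 is either undefined or describes mrTRG 2 alone, and is not the accuracy of mrTRG

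*Protocol article*

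**What the plan says.** The protocol article lists "Accuracy of mrTRG (positive predictive value and negative predictive value") as item 4 under Secondary study endpoints. The shorter list under Secondary outcomes measures has "Factors affecting complete remission and the accuracy of mrTRG".

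At restaging, two radiologists "independently assessed the response to CRT on post-CRT MRI using mrTRG (1–5) according to published definitions" (Preoperative restaging). Entry is then limited to the two best grades. Study population says that patients with "an mrTRG grade 1 or 2 based on post-CRT images will be eligible for the study", and Randomization and data management says that "the participants with mrTRG 1 or 2 tumor will be assigned using random-number table with sealed envelopes". The same section adds: "According to mrTRG 1 or 2, the allocation sequence will be stratified".

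The article uses mrTRG as a test in two ways. The Background takes grade 1 as the predictor: "a status of mrTRG1 predicted a pathologic complete remission (pCR) with 60.6% accuracy". The Discussion treats both enrolled grades as the good result: "patients with a favorable response (mrTRG 1 or 2) after pre-CRT". Item 4 does not say which cut-off or which pathological target it means.

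**The concern.** An NPV needs patients who test negative and whose true state is then established. The design admits patients because their MRI is favourable, so most or all of the negative side of the test is left outside the trial. An NPV reported from this cohort under the name of accuracy of mrTRG would be read as applying to everyone restaged after chemoradiotherapy, which it could not do.

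A second question concerns the reference standard. LE removes the scar with a margin (Investigational treatment of the experimental arm), while the Discussion attributes regional node clearance to TME. If complete remission is meant to include the nodes, the two arms do not verify it equally.

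**Working it through.** The article states no target value or precision for PPV or NPV, so there is no figure to reproduce. The check is whether each quantity has a denominator, and what it then describes.

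**Inputs from the article:** grades eligible and randomised, 1 and 2; planned enrolment 140 (Sample size calculation), so about 70 per arm; stratification by grade 1 versus 2.

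**Definition:** NPV = test negatives without complete remission ÷ all test negatives.

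**Cut-off A, positive = mrTRG 1 or 2** (the selection rule and the Discussion's favourable response). Test negatives are grades 3 to 5, of which 0 of 140 are enrolled. NPV = 0/0, undefined. PPV is estimable.

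**Cut-off B, positive = mrTRG 1** (the Background's use). Enrolled test negatives are the grade 2 patients. With n₂ patients in grade 2 and n₃₋₅ in grades 3 to 5, and complete remission rates r₂ and r₃₋₅:

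- NPV in restaged patients = [n₂(1 − r₂) + n₃₋₅(1 − r₃₋₅)] ÷ (n₂ + n₃₋₅)
- NPV from this trial = 1 − r₂

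The trial observes nothing on n₃₋₅ or r₃₋₅, so the first expression cannot be recovered from the second. What the trial can give is shown below with Wilson 95% intervals (counts rounded). The grade 2 share (40 to 75% of 140, so 56 to 105 patients) and r₂ (20 to 50%) are assumptions; the article gives neither.

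| n₂ | r₂ | 1 − r₂ | 95% CI |
|---|---|---|---|
| 105 | 0.20 | 0.80 | 0.71 to 0.87 |
| 105 | 0.50 | 0.50 | 0.40 to 0.59 |
| 56 | 0.20 | 0.80 | 0.68 to 0.89 |
| 56 | 0.50 | 0.50 | 0.37 to 0.63 |

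The half-width is about 0.08 to 0.13. The figure is computable with usable precision, but it is a statement about grade 2 only.

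**Reference standard.** If the target is ypT0, both arms supply it and no problem arises. If the target is ypT0N0, let t be the ypT0 rate and q the nodal positivity among ypT0. Assume t = 0.60 and q = 0 to 0.10. The only nodal figure in the Discussion is about 10%, and it refers to ypT2. At q = 0.10:

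- nodes seen (TME): t(1 − q) = 0.60 × 0.90 = 0.54
- nodes not seen (LE), ypT0 counted as complete remission: 0.60
- arms pooled 1:1: (0.60 + 0.54)/2 = 0.57

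The overstatement is therefore 0 to 6 points in LE and 0 to 3 points pooled.

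**A further effect in the same direction, not quantified.** LE patients with risk features who decline TME are taken out of the study (Investigational treatment of the experimental arm). They are not complete remissions, so removing them also raises PPV in LE.

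**The case against.** The strongest reply is that NPV does exist. Item 4 names no cut-off, the article's own predictive use of mrTRG is grade 1 against pathological complete remission, and both grades are recorded as a stratification factor. That stands. A reader might infer that NPV cannot be estimated at all, or that the whole endpoint fails; the article does not support either. PPV is available under both cut-offs, and NPV is available under one of them. What remains is that this NPV covers grade 2 alone.

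It may also be said that cut-off and reference standard are details an article leaves to the full protocol or analysis plan. That is fair, and their absence is not the point here. Whatever those documents say, they cannot supply grade 3 to 5 patients whom the eligibility rule keeps out. Read literally, the modified ITT set under Data analysis takes in everyone given chemoradiotherapy, which could suggest that other grades are included. Eligibility and randomisation do not support that reading.

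On the reference standard, a reader might infer that nodal status is unknown in the whole LE arm, about 70 of 140. That goes too far, because some LE patients proceed to TME. Purely as an illustration, the Background's projected completion rate of 25.6% for mrTRG 1 would give 0.256 × 70 ≈ 18 with nodes examined and about 52 without; actual uptake is unknown. However, the features that lead to completion TME in the treatment and Safety sections start at ypT2, so LE patients with ypT0, the ones who would be counted as complete remissions, would not be sent to TME under those rules.

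Finally, item 4 neither defines remission as including nodes nor says that the arms will be pooled. This part is therefore conditional, and its size is modest.

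**Conclusion.** The endpoint and the enrolled population do not match. With grade 1 or 2 as positive, the NPV denominator is 0 of 140. With grade 1 as positive, NPV is computable but applies to mrTRG 2 alone, so it is not the NPV of mrTRG among restaged patients. Overall accuracy is restricted in the same way. This follows from the eligibility rule and needs no assumption.

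The nodal part holds only if complete remission includes nodes and the arms are pooled. It is then worth about 0 to 3 points on PPV, resting on the assumed 60% ypT0 and 0 to 10% nodal positivity.

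The point affects one secondary endpoint and leaves the primary comparison, the sample size and the allocation untouched. It should be corrected because the remedy is cheap and an uncorrected figure would invite a wider claim than the cohort can carry.

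**What to change.** Replace item 4 by two descriptive estimates:

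- the proportion with ypT0 in mrTRG 1 and in mrTRG 2 separately, using both arms, each with a 95% CI;
- the proportion with ypT0N0 among patients who have TME. Show completion TME after LE separately, since those patients reach TME because of an unfavourable specimen.

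Drop NPV and overall accuracy. If they are kept, label them as mrTRG 1 versus mrTRG 2 against ypT0 within the enrolled mrTRG 1/2 population. Word the matching line under Secondary outcomes measures in the same way.

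As a guide to precision, at an assumed 60% and with all grades together, the 95% half-width is 1.96 × √(0.6 × 0.4/134) = 0.083 for ypT0 in both arms and 1.96 × √(0.6 × 0.4/67) = 0.117 for ypT0N0 on 67 TME patients. Grade-specific intervals will be wider.

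The cost is endpoint wording only. The trial gives up a general accuracy claim that this cohort cannot support.
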